## Abstract

**Background:**

Head injury in older adults is increasingly common, often caused by low-impact falls. A significant proportion of these patients are taking oral anticoagulants (OACs) to prevent stroke or thromboembolism. When traumatic bleeding within the head occurs, OACs are usually stopped to reduce the risk of worsening haemorrhage; however, prolonged interruption increases the risk of stroke, systemic thromboembolism and death. There is currently no consensus on when it is safest to restart OACs. Direct oral anticoagulants (DOACs) are now widely prescribed and may offer advantages over warfarin. This trial aims to determine the safest and most effective timing to start/restart a DOAC after a traumatic intracranial haemorrhage (tICH).

**Methods:**

This is a phase III, multi-centre, randomised controlled trial. Adults with tICH who were taking an OAC before injury will be recruited across approximately 20 trauma networks in the UK. Eligible participants will be randomised to restart DOAC therapy either 1 week or 4 weeks after tICH. The primary outcome is the proportion of patients with a haemorrhagic or thrombotic event within 12 weeks of tICH. Secondary outcomes include time-to-first haemorrhagic or thrombotic event, survival, functional status, quality of life and health resource use. Follow-up will occur at 6, 12 and 26 weeks, with data analysed on an intention-to-treat basis. Health economic and qualitative sub-studies will run alongside the main trial.

**Discussion:**

This study addresses a major area of clinical uncertainty. By directly comparing 1-week versus 4-week re-initiation of OAC, this trial will provide robust evidence to guide clinical practice in a tICH population at high risk of both bleeding and thrombotic complications. Findings will inform patient counselling, acute care protocols and guideline development.

**Ethics and dissemination section:**

Ethical approval has been obtained from the Berkshire Research Ethics Committee (24/SC/0298). Written informed consent will be obtained from all participants or their legal representatives before enrolment. Findings will be disseminated through peer-reviewed publications, scientific conferences, trial registry reporting and patient-facing summaries, with the aim of informing future guidance on anticoagulation management following tICrH.

**Trial registration:**

NCT06322953.

STRENGTHS AND LIMITATIONS OF THIS STUDYMulticentre, pragmatic randomised controlled trial evaluating the optimal timing of direct oral anticoagulant resumption after traumatic intracranial haemorrhage.Includes clinical, functional, quality-of-life, health economic and qualitative outcomes.Patient and public involvement informed the study design and outcome selection.Open-label design may introduce bias, although it reflects routine clinical practice.Findings may not be generalisable to patients requiring long-term vitamin K antagonist therapy or those with mechanical heart valves.

## Introduction

 Head injury in older adults is increasingly common. In the 2017 review of trauma networks in England and Wales, a fall from standing height in an older person was the most common mechanism of major trauma and most often resulted in head injury (these data excluded isolated neck of femur and distal limb fractures).^1^ With one in six people projected to be aged ≥65 years by 2050, and around 30% of older adults falling each year, the incidence of head injury will continue to increase.^2
3^ In parallel, oral anticoagulant (OAC) use has grown because atrial fibrillation (AF)—whose prevalence rises with age—increases stroke risk about five-fold and merits OAC based on stroke risk, commonly assessed using the CHA_2_DS_2_VASc or CHA_2_DS_2_VA clinical risk scores.^4
5^

OAC prescribing in the UK has more than doubled since 2000,^6^ and 20–35% of older patients admitted with traumatic intracranial haemorrhage (tICrH) are taking an OAC at the time of injury.^7
8^ Standard practice is to stop OAC acutely to mitigate early haemorrhage expansion; however, despite the low risk of new or ongoing intracranial bleeding after 48 hours, clinicians are often reluctant to restart OAC because of rebleeding concerns. This must be balanced against the increased risk of stroke, systemic thromboembolism and death when anticoagulation is withheld.^9
10^ There is no clear consensus on optimal timing for restarting OAC after tICrH and a 2021 survey of UK neurosurgeons reported that most advise restarting OACs at 1–4 weeks following tICrH.^6^ A live poll during a virtual UK neurosurgical conference confirmed acceptability of early (1 week) compared with late (4 weeks) and this is also supported by a proposed trial design by an American study group which included 1, 2 and 4 week restart times.^7^

One recent trial assessing patients with major bleeding on anticoagulation reported re-bleeding rates of 4.3% within 30 days when excluding the first 3 days after the initial bleed.^8^ Importantly, the bleeding rate was only 4.5% among those who restarted anticoagulation within 2 weeks compared with those who did not restart within the same timeframe. Another study focusing specifically on tICrH observed a 5% readmission rate for re-bleeding within 30 days in patients who did not restart their direct oral anticoagulant (DOAC).^11^ Despite these findings, there remains a paucity of high-level data describing delayed (>72 hours) haemorrhage rates after tICrH.

OAC medications are generally divided into vitamin K antagonists (eg, warfarin) and DOACs. DOAC use has risen substantially over the past decade given the advantages of rapid starting, fixed dosing, fewer drug interactions and no routine monitoring compared with warfarin.^12
13^ Trials and meta-analyses show that DOACs are at least as effective as warfarin for stroke prevention in AF, with lower rates of intracranial haemorrhage and mortality.^14^ Similar evidence for efficacy and safety is available for venous thromboembolism.^15^

This trial will focus on patients prescribed a DOAC or warfarin for atrial fibrillation or venous thromboembolism at the time of tICrH whose OAC is stopped acutely. Patients will either restart their DOAC or, if on warfarin or another vitamin K antagonist (VKA), be offered a switch to a DOAC in line with best practice and the superior safety profile of DOACs after intracranial haemorrhage.^16^

## Methods and analysis

### Objectives

Our primary objective is to compare the clinical effectiveness (a reduction in thrombotic events outweighing any increase in haemorrhagic events) of restarting or initiating a DOAC at 1 week versus 4 weeks following tICrH. Secondary objectives are to evaluate the effect of early versus late anticoagulation restart on (1) timing of haemorrhagic/thrombotic events and survival; to better understand how events relate to the original head injury and DOAC timing; (2) functional status and health-related quality of life with measures relevant to long-term recovery in the older head injury population; and (3) qualitative data on patient and caregiver attitudes. The primary economic objective is to estimate cost-effectiveness. A summary of the study outcomes and their definitions is provided in table 1.

**Table 1 T1:** Primary and secondary outcomes

Outcome	Definition / Measurement	Timepoint
Primary outcome		
Proportion of patients experiencing a haemorrhagic or thrombotic event following traumatic intracranial haemorrhage.		12 weeks
Event definition*	Haemorrhagic events: (i) haematoma expansion or new intracranial haemorrhage on CT/MRI; (ii) change in clinical status (altered conscious level, new or progressing neurological deficit); and (iii) cessation of anticoagulation if already restarted. Thrombotic events: venous thromboembolism, myocardial infarction, ischaemic stroke, systemic embolism or non-bleeding cardiovascular death.	—
Secondary outcomes		
Time to first haemorrhagic or thrombotic event	Time (days) from randomisation to first qualifying event.	Up to 12 weeks
Time to first haemorrhagic event	Time (days) from randomisation to first haemorrhagic event.	Up to 12 weeks
Time to first thrombotic event	Time (days) from randomisation to first thrombotic event.	Up to 12 weeks
Survival	Time from randomisation to death from any cause.	Up to 26 weeks
Functional outcomes	Simplified Modified Rankin Scale, Barthel Index, Extended Glasgow Outcome Scale and Rockwood Frailty Score.	12 and 26 weeks
Quality of life	EQ-5D-5L scores; utilities used for health-economic evaluation.	6, 12 and 26 weeks
Patient and caregiver attitudes	Semi-structured interviews exploring views on starting or restarting oral anticoagulation.	Within 60 days
Healthcare resource use	Hospital, community and social-care utilisation derived from case report forms and routine data linkage (eg, Hospital Episode Statistics).	6, 12 and 26 weeks
Economic Outcome		
Cost-effectiveness	Incremental cost per quality-adjusted life year (QALY) gained	Lifetime

* Events are determined by the clinical team caring for the patient.

### Patient and public involvement

Patients and caregivers were involved in formulating the study question and informing the study design. There was clear consensus that both preventing a stroke and re-bleeding were to be avoided which informed the decision to use a composite primary endpoint. All patients were happy to be randomised to restarting a DOAC at week 1 or week 4. There was a clear preference for remote follow-up by phone, post or email. Legal representative consent will be used in cases where the patients lack capacity to consent. Two patients with lived experience of taking DOAC are members of the trial management group and will contribute to ongoing trial oversight, participant-facing materials and interpretation of findings. Their involvement will ensure that the study remains aligned with patient priorities, supports acceptable recruitment and retention strategies and enhances the relevance and accessibility of trial outputs. Public and patient involvement (PPI) contributors will also be involved in dissemination activities, including development of lay summaries and communication of results to participants and the wider public.

### Trial design

This trial is designed as a multicentre, pragmatic, parallel-group, two-arm, superiority, randomised controlled trial (RCT), with 1:1 allocation ratio, stratified by recruitment site, injury severity (Glasgow Coma Score >12 or ≤12) and frailty assessed via the Rockwood Clinical Frailty Scale (0–4 or 5–9). The study is a Type A CTIMP (Clinical Trial of Investigational Medicinal Product): no higher than that of standard medical care. Participants will be identified and recruited across at least 20 trauma networks in the UK (https://restart-trial.org.uk). Eligible participants are adults with tICrH who were receiving oral anticoagulation as part of their routine medications prior to admission, regardless of when the last dose was taken. Full inclusion and exclusion criteria are summarised in table 2.

**Table 2 T2:** Eligibility criteria for participation in the trial

Category	Criteria
Inclusion criteria	Informed consent obtained from participant or participant’s legal representative and ability to comply with the requirements of the trial. Adults ≥18 years with traumatic intracranial haemorrhage (tICrH) within the past 1 week who were taking an OAC prior to admission. Oral anticoagulants include any direct oral DOAC or VKA (eg, warfarin), prescribed for AF or VTE prior to admission for tICrH.
Exclusion criteria	Traumatic intracranial haemorrhage limited to chronic subdural haematoma only. Patients with a mechanical heart valve. Plan to start/restart antiplatelet therapy within 12 weeks of tICrH. Abbreviated Injury Scale other than head with a score >3. Pregnant or breast-feeding female. Participants of reproductive potential (male or female) unwilling to use a reliable means of contraception. Hypersensitivity or contraindication to DOAC as detailed in the Investigational Medicinal Product Summary of Product Characteristics (SmPC). Ongoing bleeding where it would be unsafe to restart DOAC at 1 week. Clinical reason requiring DOAC restart before 4 weeks or beyond the 12-week study period. Indication to remain on VKA rather than switching to DOAC (eg, severe renal impairment or mechanical heart valve).

AF, atrial fibrillation; DOAC, direct oral anticoagulant; OAC, oral anticoagulant; VKA, vitamin K antagonist; VTE, Venous Thromboembolism.

### Intervention and comparator

Adults with tICrH who require OAC will be randomised to re/start a DOAC either 1 week or 4 weeks after the index haemorrhage. The specific DOAC (eg, apixaban, dabigatran, edoxaban, rivaroxaban) and dose will be prescribed as part of usual care according to the patient’s prior prescription or local hospital policy. The trial does not mandate a particular agent if switching from warfarin or other VKA. Sites will verify that participants initiate DOAC at the allocated time point and ascertain whether doses have been missed at each follow-up. Participants (or a legal representative) can receive reminders to re-start by text message, email, phone or video call, as per their preference.

Discontinuation or modification of DOAC therapy is determined on clinical grounds by the local medical team; participants remain in the trial and reasons are recorded on the electronic case report form. Prespecified circumstances prompting treatment cessation include adverse events, use of prohibited medication, pregnancy or any condition that in the investigator’s judgement jeopardises participant safety.

### Qualitative sub-study

An embedded qualitative sub-study will explore patient and caregiver attitudes to recommencing a DOAC following tICrH to support understanding and communication of final study findings to both clinicians and patients and identify knowledge gaps for future research. A PPI focus group of 6–8 tICrH survivors and caregivers will be undertaken to inform the topic guide as there is currently limited qualitative data available in this patient group.^17^ Purposive sampling will be undertaken to obtain 10–20 patients and/or caregivers (of those patients lacking capacity to consent) to represent diversity in terms of site, age, gender, ethnicity, presence of a caregiver and other patient characteristics (PROGRESS+criteria).^18^ Participants who decline (n=10 patient/caregivers) will also be invited to take part to discuss reasons for declining a DOAC and to inform patient-clinician discussions regarding treatment options. Individual semi-structured interviews will be undertaken, data collection will continue until saturation is reached, prior to thematic framework analysis.^19^

### Harms and event reporting

Anticipated risks reflect the clinical trade-off inherent in restarting anticoagulation after tICrH and include recurrent or progressive intracranial haemorrhage and extracranial bleeding versus thrombotic events if anticoagulation is withheld. Safety events will be reported from consent to the last study visit (week 26 or premature discontinuation). Related adverse events will be collected for this trial; haemorrhagic or thrombotic events that constitute prespecified trial endpoints are captured as outcomes and will not be duplicated as adverse events. Thrombotic events are determined by imaging initiated by clinicians on the basis of patient symptoms and clinical suspicion as part of routine care, rather than any pre-determined screening. As these are outcome events they will be screened for at all follow-up points with the research team but do not require immediate reporting. Haemorrhagic events are also determined by imaging initiated by clinicians; however, to avoid over-reporting of minor or insignificant imaging changes, must also be accompanied by a clear clinical concern with new neurological symptoms or altered conscious level. In the case of patients who have restarted their DOAC this must also be considered significant enough that the clinician wishes to stop the DOAC. There is no central adjudication or pre-specified determinants of haemorrhagic events and the study relies on pragmatic clinician-led decision making.

All events meeting the definition of a serious adverse event must be reported to the coordinating centre within 24 hours of site awareness. All reportable adverse events will be graded for severity (mild: no interference with routine activities; moderate: interferes with routine activities; severe: impossible to perform routine activities; life-threatening; death). The following are not recorded as adverse events: non-serious events that are unrelated; medical/surgical procedures per se (record the underlying condition instead); pre-existing conditions that do not worsen; situations without an untoward medical occurrence (eg, elective cosmetic surgery); overdose without signs or symptoms (though this may still prompt safety follow-up to ensure regulatory compliance). If overdose leads to an event meeting, it will be reported accordingly and highlighted to the coordinating centre.

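### Non-serious extracranial bleeds are recorded only if unblinded sites judge them related, so their comparison between arms in weeks 1-4 is probably not like for like

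*Protocol article*

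**What the plan says.** The rule is in the protocol article under Harms and event reporting, and it appears there twice. First: "Related adverse events will be collected for this trial". Then, in the list of exclusions: "The following are not recorded as adverse events: non-serious events that are unrelated". Neither sentence says what the event must be related to.

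The same section names the anticipated risks as "recurrent or progressive intracranial haemorrhage and extracranial bleeding versus thrombotic events if anticoagulation is withheld", so extracranial bleeding is an expected harm.

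Two kinds of event do not pass through the relatedness filter:

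- Serious events: "All events meeting the definition of a serious adverse event must be reported to the coordinating centre within 24 hours of site awareness". No relatedness condition is attached.
- Endpoint events: "haemorrhagic or thrombotic events that constitute prespecified trial endpoints are captured as outcomes and will not be duplicated as adverse events". In Table 1, however, the imaging component of the haemorrhagic event is "haematoma expansion or new intracranial haemorrhage on CT/MRI", so an extracranial bleed is not an endpoint event.

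Under Intervention and comparator, participants are "randomised to re/start a DOAC either 1 week or 4 weeks after the index haemorrhage". The Blinding section states that participants, treating clinicians, site research staff and outcome assessors are all unblinded. Safety reporting runs from consent to the last study visit at week 26, in both arms.

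**The concern.** Randomisation sets when DOAC exposure begins. Between weeks 1 and 4 the early arm is assigned to be on drug and the late arm off it. A causality judgement depends on exposure, so a filter based on causality can act differently in the two arms during exactly the period in which they differ. A nosebleed in week 2 is easily called related in a participant who has restarted. It is less easily called related in one who has not, and it is then not recorded. The site knows the allocation in both cases.

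The shared window from consent to week 26 does not cure this, because the filter works inside the window. Nor does the article describe another route by which a non-serious extracranial bleed would reach the data.

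What is at stake is a secondary but visible part of the harm picture. The article's Discussion (in the Abstract) says the findings will inform patient counselling and guidelines, and bleeding is the feared cost of early restart. Recruitment is under way, and minor bleeds that were never recorded are hard to recover later.

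**Working it through.** The plan gives no figure to reproduce here, because the point concerns a recording rule. The check has two steps.

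**Step 1: which route does each type of event take into the data?**

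| Event | Route | Depends on relatedness? |
|---|---|---|
| Endpoint haemorrhagic or thrombotic event | Outcome data (Table 1) | No |
| Serious extracranial bleed | Serious adverse event report | No |
| Non-serious extracranial bleed | Adverse event record | Yes |

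Of these three, only the last depends on the judgement.

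**Step 2: how large could the artefact be if there were no true difference?**

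Inputs from the article: DOAC starts at week 1 or week 4, the primary outcome is at 12 weeks, and safety reporting runs to week 26.

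Assumptions, none of which the article gives:

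- The true weekly rate of non-serious extracranial bleeding is equal in the two arms and constant over time.
- Participants start at the allocated time.
- A share q of bleeds is judged related while on DOAC, and a share s while off it.

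From week 1 to week H, the early arm has H - 1 weeks on drug. The late arm has 3 weeks off drug and H - 4 weeks on. The recorded ratio, early to late, is

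R(H) = q(H - 1) / [3s + q(H - 4)].

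*Limiting case, s = 0.* The share q cancels and R(H) = (H - 1)/(H - 4).

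- Weeks 1-12: 11/8 = 1.375.
- Weeks 1-26: 25/22 = 1.14.
- Weeks 1-4: the late arm records nothing, so the ratio is undefined.

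*Partial capture, q = 0.5:*

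| s | Weeks 1-4 | Weeks 1-12 | Weeks 1-26 |
|---|---|---|---|
| 0.05 | 1.5/0.15 = 10.0 | 5.5/4.15 = 1.33 | 12.5/11.15 = 1.12 |
| 0.25 | 1.5/0.75 = 2.0 | 5.5/4.75 = 1.16 | 12.5/11.75 = 1.06 |

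*No differential judgement, s = q.* R(H) = q(H - 1)/[q(H - 1)] = 1.00 at every horizon.

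*All bleeds recorded, q = s = 1.* R(H) = 1.00 at every horizon.

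**Absolute ceiling.** Suppose 1%, 3% or 5% of participants had such a bleed in weeks 1-4 (assumed), all recorded in the early arm and none in the late arm. With 487 per group the excess would be 487 x 0.01 = 5, 487 x 0.03 = 15 or 487 x 0.05 = 24 participants. These are upper limits at each assumed rate. With q = 0.5 and s = 0 they halve.

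**The case against.** The strongest reply is that the article says only related, not related to the DOAC. The intervention is a restart time, and the listed risks include thrombosis while anticoagulation is withheld, so relatedness to the allocated strategy is a possible reading. The definition may well stand in the full protocol, which is not shown. This stands as a limit on certainty. It does not remove the problem, since the trial is a trial of a medicinal product and causality is most naturally judged against that product.

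A reader might infer that the late arm will have almost no non-serious events on record before week 4. The article does not support this. It follows only if sites call every off-drug event unrelated, and no section says so.

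A reader might also infer that the safety comparison as a whole is biased against early restart, or that the primary objective is distorted. Neither follows. Serious events are reported in both arms without a relatedness condition, and endpoint events are captured as outcomes. Non-serious extracranial bleeds are not part of the composite. The net direction across all safety data is not settled either: after restart, a haemorrhagic endpoint event also requires that the clinician wishes to stop the DOAC, and that tends to lower the early arm's count in weeks 1-4.

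It is also fair to say that leaving out unrelated non-serious events is a coherent choice for a pragmatic, low-risk trial of drugs given as usual care, and that the article specifies no between-arm test of adverse events. Both points keep the matter modest. Neither makes the recorded counts comparable for a harm the article names.

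**Conclusion.** The point holds in a narrow form. Non-serious extracranial bleeding is recorded only through an unblinded relatedness judgement. If that judgement is made against the DOAC, the comparison between arms in weeks 1-4 is not like for like and probably leans against early restart.

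Over the full reporting window the artefact is small to moderate. The early-to-late ratio is at most about 1.38 over weeks 1-12 and 1.14 over weeks 1-26, and 1.00 if sites judge alike on and off drug. These bounds assume equal true rates, a constant weekly rate, starts at the allocated time, and off-drug bleeds called related no more often than on-drug bleeds. If minor bleeds cluster in weeks 1-4, the ratios could be higher. The absolute counts rest on assumed rates and are ceilings.

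Serious adverse events, endpoint events and the primary analysis are not touched. This is an inexpensive improvement to data capture and not a threat to the trial's main conclusion.

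**What to change.** Record every extracranial bleeding event, serious or not, in both arms from randomisation to week 26 regardless of causality. One item on the existing 6, 12 and 26 week forms, with the date of the bleed, would do this. Tabulate the events by allocated arm over the same window. Keep the relatedness filter for all other non-serious events, and amend the wording under Harms and event reporting to state the exception.

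The cost is a protocol wording change, one form item and slightly more data entry at sites. The remedy is partial: in an open-label trial, participants and staff who know a DOAC is being taken may still notice and report minor bleeds more readily. It does remove the part of the difference that the recording rule itself creates. Because recruitment is under way, the change should be made soon, and participants followed up before it should be identifiable in the tabulation.
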